## Abstract

**Background:**

Evidence linking exposure to airborne particulate and gaseous pollutants, as well as mold spores, with asthma control and severity is well established. A growing body of literature has demonstrated that ventilation and air filtration can improve indoor air quality (IAQ); however, clinical evidence on their comparative health impacts remains limited. Therefore, this trial aims to evaluate the long-term effectiveness of energy recovery ventilators (ERVs) and portable air cleaners (PACs) in reducing indoor air pollutants and mold levels and improving health outcomes in individuals with asthma. Secondary objectives includes associations between housing conditions, occupant behaviors, indoor environmental exposures, and asthma-related health outcomes.

**Methods:**

The AIRVAC study is a single-blind, placebo-controlled, 4-arm, parallel-group, randomized controlled trial, with a pre-intervention period of up to 1 year and a 1-year post-intervention period. Children aged 5–17 years and adults with physician-diagnosed asthma will be recruited from more than 80 households across the Dallas-Fort Worth (DFW) area in Texas. Following the pre-intervention period, each household will be randomized to receive one of four different interventions midway through the study: (1) active ERVs, (2) sham ERVs, (3) active PACs, and (4) sham PACs. Primary health outcomes include asthma control; secondary outcomes include pulmonary function, asthma-related quality of life, stress, and sleep quality. Initial housing assessments will be conducted prior to the pre-intervention period to characterize occupant behaviors and housing-related factors that may contribute to asthma exacerbations and affect ERV installation. Environmental exposures will be assessed by combining measurements of indoor and outdoor air pollutants, including particulate matter (PM), nitrogen dioxide (NO_2_), carbon monoxide (CO), and volatile organic compounds (VOCs), as well as temperature, relative humidity, and indoor and outdoor mold, using low-cost and research-grade air quality sensors and mold sampling methods.

**Discussion:**

Findings from the AIRVAC study will provide important evidence on the comparative effects of residential ventilation and air cleaning interventions on IAQ, mold, and asthma-related health outcomes among children and adults with asthma. The study will also examine the relationships among housing characteristics, occupant behaviors, indoor environmental exposures, and asthma-related health outcomes, while providing insights into the operation and performance of residential ventilation and air cleaning interventions in vulnerable households.

## Introduction

Asthma is an allergic respiratory disease characterized by airway inflammation, mucus accumulation, and bronchoconstriction, resulting in reduced airflow. Common symptoms include wheezing, shortness of breath, chest tightness, and coughing, which can range in severity from mild to severe [1,2]. Asthma affects approximately 300 million people worldwide [3], and nearly 27 million Americans have been diagnosed with asthma, including 4.5 million children and 22.3 million adults [4]. The annual economic burden of asthma in the United States is estimated to be approximately $82 billion, including medical care, medications, hospitalizations, lost work and school days, and mortality-related costs [5].

Air pollution is one of the major triggers and determinants of asthma, influencing both disease onset and exacerbation across age groups, particularly in residences where people spend most of their time indoors [6]. Exposure to pollutants such as particulate matter (PM), nitrogen dioxide (NO_2_), volatile organic compounds (VOCs), and carbon monoxide (CO), induces oxidative stress and airway inflammation that lead to epithelial injury, bronchial hyperresponsiveness, and airway remodeling [7–10]. Particularly in residences where individuals spend most of their time indoors, combustion sources such as gas stoves, tobacco smoke, and unvented heating appliances can generate pollutant concentrations that exceed acute or chronic health standards, resulting in asthma attacks and exacerbations [11–14]. Further, indoor dampness and mold can exacerbate asthma through the release of spores and mycotoxins from species such as *Aspergillus* and *Cladosporium*, which disrupt epithelial integrity and provoke IgE-mediated and Th2-driven inflammation [15,16].

Ventilation and air cleaning are widely recognized and well-established strategies for effectively reducing indoor air pollutants when controlling or eliminating the source of the pollutants is impractical as a remedial measure [17]. Balanced ventilation systems, often integrated with energy recovery ventilators (ERVs), simultaneously introduce filtered outdoor air and exhaust stale indoor air, diluting both particulate and gaseous pollutants while maintaining neutral air pressure within the building for optimal air exchange. ERVs can be equipped with Minimum Efficiency Reporting Value (MERV) 8 or higher filters to remove particles, allergens, and other contaminants from incoming outdoor air. Air cleaners, also known as stand-alone air filtration systems, primarily remove airborne pollutants from indoor air. High-efficiency particulate air (HEPA) filtration can remove at least 99.97% of particles with diameters of 0.3 µm, while gas-phase filtration (e.g., activated carbon filters) can adsorb some gaseous pollutants, including VOCs and odors.

Substantial empirical evidence supports the effectiveness of mechanical ventilation systems in improving indoor air quality (IAQ) in homes [18–25]. Although several clinical studies have further investigated the effects of residential ventilation systems on asthma-related health outcomes [26–31], none of these studies comprehensively assessed IAQ, including particulate and gaseous pollutants, mold, as well as temperature and humidity, and only one trial implemented a true placebo control; the others either provided no intervention to controls or had no control group. Similarly, a growing body of literature has shown that residential HEPA air cleaners can lower indoor PM and allergens and yield at least modest health benefits for a variety of populations, including individuals with asthma [17,32,33]. However, important knowledge gaps remain, including small sample sizes, short-term intervention periods, and variability in outcome measures.

### Objectives and hypotheses

The primary objective of this study is to evaluate the comparative long-term (one-year) effects of ERVs and portable HEPA air cleaners on reducing exposure to indoor particulate and gaseous pollutants and mold, as well as on improving asthma-related health outcomes in inner-city children and adults with asthma in the Dallas-Fort Worth (DFW) area of Texas. We hypothesize that year-long use of ERVs and portable HEPA air cleaners will lead to improvements in IAQ and asthma-related health outcomes during the post-intervention period compared to the pre-intervention period, whereas control groups are expected to show no significant changes. Further, we hypothesize that two interventions will differ in both the profiles and magnitudes of IAQ and health improvements, as ERVs are designed to reduce both particulate and gaseous pollutants and help control indoor humidity to lower the risk of mold growth, whereas HEPA air cleaners primarily remove airborne particles from indoor air.

## Methods

The analysis and reporting of trial findings will adhere to the Consolidated Standards of Reporting Trials (CONSORT) extension for cluster randomized trials and will be guided by a pre-specified statistical analysis plan. The Asthma Intervention with Residential Ventilation and Air Cleaner (AIRVAC) study was approved by the Institutional Review Board (IRB) of the University of Texas at Arlington (UTA) Office of Regulatory Services (IRB #2025-0280; approval date: 08/01/2025). Written informed consent will be obtained from all participants (or their legal guardians, as applicable) prior to enrollment and any study procedures during the initial home visit (V0), in accordance with institutional ethical guidelines. Participant confidentiality will be maintained by assigning unique study identification numbers to participants and securely storing all study data with access limited to authorized research personnel. The study is registered at ClinicalTrials.gov (NCT07196436; registration date: 9/29/2025). The recruitment period for this study is from September 2025 to September 2026; recruitment is ongoing at the time of writing. Data collection has not yet begun and is expected to be completed by February 2028, with study results anticipated in April 2028.

### Study design

The AIRVAC study is a single-blind, placebo-controlled, four-arm, parallel-group, randomized controlled trial ERVs and portable HEPA air cleaners, with a pre-intervention period of up to 1 year and a 1-year post-intervention period. The pre-intervention period was designed to characterize baseline variability in indoor environmental conditions and health outcomes across seasons and to account for seasonal variations in longitudinal analyses using time-related covariates. Participants will be randomly assigned to one of four groups: (1) active ERV, (2) sham (placebo) ERV, (3) active portable HEPA air cleaner, or (4) sham (placebo) portable HEPA air cleaner.

The study involves five home visits. During the initial home visit (V0), the field team, which includes a BPI Building Analyst Professional (BAP)-certified investigator [34] and a licensed HVAC contractor, will conduct initial home visits (V0) to obtain information on housing conditions, health and safety concerns, and potential asthma triggers that may contribute to exacerbations or affect ERV installation. Key parameters to be assessed include home size, construction type, heating, ventilation, and air conditioning (HVAC) system, window operation, kitchen stove and hood, occupant behaviors, and other environmental risk indicators (e.g., visible mold, water damage, asbestos, chipping paint, pests, and pets). Additionally, for homes deemed eligible following the health and safety evaluation, blower door tests will be performed to measure the airtightness of the building envelope.

Following the initial visit, four follow-up visits (V1-V4) will be conducted to assess environmental exposures and health outcomes (two during the pre-intervention period and two during the post-intervention period). Fig 1 shows an overview of the study visit timeline with tasks that will be performed at each visit.

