### Data management and statistical analysis plan

The full data collection will include three categories of data: (1) human subject data, including demographic and socioeconomic characteristics and asthma-related health outcomes collected via baseline and follow-up questionnaires; (2) housing characteristics, including building and dwelling information; and (3) environmental exposure data, including indoor and outdoor air quality and mold measurements. All data will be de-identified prior to analysis to protect participant confidentiality, with direct identifiers removed before sharing. Data will be stored as comma-separated text files and spreadsheet files on a secure central server in the PI’s laboratory and processed electronically using Stata or Python in appropriate analysis formats. De-identified data will be shared only with the PI. Missing data will be handled using multiple imputation under the missing-at-random assumption, where collected data will be used to predict missing values. At least 20 imputed datasets will be generated, and convergence diagnostics and comparisons between observed and imputed data will be performed to assess plausibility [51]. Mixed-effects models for repeated measures will be used to account for within-subject correlations, and sensitivity analyses will compare complete-case and multiple imputation results.

Descriptive statistics will summarize participant demographics (e.g., age, sex, race/ethnicity, household income) and study variables by group, with continuous variables presented as means, medians, standard deviations, interquartile ranges (IQRs), or other distributional parameters, and categorical variables as frequencies and percentages. Appropriate statistical tests will be applied based on data type and distribution, including paired and unpaired t-tests, Wilcoxon signed-rank or rank-sum tests, and chi-square tests for categorical comparisons.

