The primary analyses will follow the intention-to-treat (ITT) principle, including all randomized households analyzed according to their assigned intervention group, to evaluate the effects of ERVs and portable HEPA air cleaners on IAQ, mold reduction, and asthma-related health outcomes by comparing the intervention and control (sham) groups using repeated measures analysis of variance (ANOVA) with a within-between interaction. Pairwise comparisons will be conducted between each intervention and control group (Group 1 vs. Group 2, Group 3 vs. Group 4) and between intervention groups (Group 1 vs. Group 3), using Tukey’s Honest Significant Difference (HSD) test to adjust for multiple comparisons. Repeated monthly ACT scores will be analyzed using multivariate mixed-effects models to account for within-subject correlations over time. Per-protocol (PP) analyses will be conducted as sensitivity analyses and will include only households that adequately adhered to the assigned intervention protocol. Intervention adherence will be assessed using plug load logger data for both ERV and air cleaner units, including device operation status and operating duration [52]. Additionally, subgroup analyses will be conducted to explore whether intervention effects differ by demographic and socioeconomic characteristics, baseline asthma severity, and baseline IAQ.

For secondary analyses, multivariate linear and logistic regression models will examine associations among housing characteristics, occupant behaviors, indoor environmental exposures (e.g., air pollutants and mold), and asthma-related health outcomes. Housing characteristics will be considered as potential covariates or confounders, when applicable, based on biological plausibility and statistical considerations. Prior to multivariable modeling, correlations among environmental exposure variables (e.g., PM, NO_2_, VOCs, and mold indices) will be evaluated using Pearson or Spearman correlation coefficients, depending on data distribution. Variance inflation factors (VIFs) will also be calculated to assess multicollinearity among predictors. Highly correlated exposures will not be included simultaneously in the same model to minimize multicollinearity, overfitting, and unstable estimates.

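### Season is to be handled by time-related covariates, but the repeated-measures ANOVA named as primary for IAQ, mold, ACQ and spirometry names none and has no natural place for one

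*Protocol article*

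**What the plan says.** The Study design section gives the pre-intervention period, of up to one year, two purposes: to describe baseline variability across seasons, and "to account for seasonal variations in longitudinal analyses using time-related covariates". It does not name the covariates.

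The Data management and statistical analysis plan section compares active with sham groups on IAQ, mold and asthma-related health outcomes "using repeated measures analysis of variance (ANOVA) with a within-between interaction". No calendar or season term is mentioned. The only model covariates discussed come in the secondary-analysis paragraph: "Housing characteristics will be considered as potential covariates or confounders, when applicable".

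The same section also refers to mixed models, once in general ("Mixed-effects models for repeated measures will be used to account for within-subject correlations") and once for a single primary outcome ("Repeated monthly ACT scores will be analyzed using multivariate mixed-effects models to account for within-subject correlations over time"). ACQ, spirometry, IAQ and mold are not assigned to a mixed model by name.

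On timing, the Methods section states: "The recruitment period for this study is from September 2025 to September 2026". It expects data collection to finish by February 2028. The post-intervention period is one year.

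**The concern.** A standard within-between ANOVA has one factor for group and one for measurement occasion. Table 1 sizes the trial on this model with 24, 4 or 2 occasions, so the time factor is most naturally read as study month or visit number. If homes start at different times of year, the same study month or visit falls in different seasons in different homes. The time factor then cannot stand in for season, and the model has no slot for a covariate that varies by home and by occasion. The stated aim for season and the stated primary model do not meet.

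Two things are at stake. One is precision in active-versus-sham comparisons with about 20 homes per arm. The other is the hypothesis in the Objectives section that outcomes improve from the pre- to the post-period while controls show no significant change. A pre-period covering only part of a year, set against a full post-year, can produce a purely seasonal change within an arm, and randomisation does not remove it from a within-arm statement.

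**Working it through.** **1. The plan's own figure.** For the within-between interaction, take λ = f²·N·m/(1−ρ), df1 = (k−1)(m−1), df2 = (N−k)(m−1), with k = 4. The article does not state ρ or sphericity; I assume ρ = 0.5 and ε = 1. For ACT/IAQ, f = 0.10, N = 76, m = 24:

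- λ = 0.01 × 76 × 24 / 0.5 = 36.48, df = 69 and 1656.
- Power is 0.815, against 0.82 in Table 1, so the figure reproduces. At N = 80 power is 0.844.

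No figure in Table 1 is shown to be wrong by this point.

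**2. How long can the pre-period be?** February 2028 minus 12 post-intervention months gives a last intervention start of about February 2027.

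- For a 12-month pre-period, V1 must fall by about February 2026.
- For a September 2026 entrant, September 2026 to February 2027 is at most about 5 months, hence at most 5 + 12 = 17 monthly values rather than 24.

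**3. Can the study-month factor absorb season?** For a yearly sine and start dates uniform over W months, the share of seasonal variance it misses is 1 − [sin(πW/12)/(πW/12)]². That is 0% for a common start, 19% for W = 3, 60% for W = 6 and 100% for W = 12.

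**4. Effect on the standard error (SE).** I use the active-minus-sham difference in before-after change as a stand-in for the interaction. Assumptions: 20 homes per arm, residual SD 1, starts spread over 12 months, seasonal amplitude A (in residual SDs), pre-period L uniform on 5 to 12 months, V4 at the end of the post-year.

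*Monthly data.* A full post-year averages season to zero, so the variance of one home's change is 1/L + 1/12 + (A²/2)·g(L), with g(L) = [sin(πL/12)/(L·sin(π/12))]². From L = 5 to 12, g is 0.557, 0.415, 0.284, 0.175, 0.092, 0.037, 0.008, 0. Rounding L to whole months (weight 1/14 at each end, 1/7 between), mean 1/L = 0.1255 and mean g = 0.184. Multiply by 2/20 and take the root:

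- A = 0: √[0.1 × (0.1255 + 0.0833)] = 0.1445
- A = 0.5: √[0.1 × (0.2088 + 0.0230)] = 0.152, +5%
- A = 1: √[0.1 × (0.2088 + 0.0922)] = 0.173, +20%

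*Single V1 versus V4 (the mold design).* The variance of one home's change is 2 + A²·2·½·2·½·[1 − mean cos(πL/6)]; that is, 2 + A²[1 − mean cos(πL/6)], with the mean cosine −0.136:

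- A = 0: √(0.1 × 2) = 0.447
- A = 0.5: √(0.1 × 2.284) = 0.478, +7%
- A = 1: √(0.1 × 3.136) = 0.560, +25%

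Simulation of the same settings (1,500 runs) gave 0.143, 0.154, 0.169 for monthly data (+8%, +18%) and 0.434, 0.479, 0.557 for V1 versus V4 (+10%, +28%). A ratio of two simulated SEs carries an error of about √2/√(2 × 1500) = 2.6%, so the two sets agree. Bias was about zero throughout.

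*Where nothing is lost.* With 12 + 12 months the simulated SEs were 0.127, 0.131, 0.128 for monthly data. With V1 and V4 exactly 24 months apart they were 0.457, 0.450, 0.445. Both are flat apart from simulation error.

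**5. Does a calendar term recover it?** I added sine and cosine of the calendar date to a fit with home effects, period and arm-by-period (3,000 runs).

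- Monthly SEs at A = 0.5 and 1 went from 0.151 and 0.167 to 0.145 and 0.145.
- V1-versus-V4 SEs went from 0.477 and 0.561 to 0.457 and 0.460.
- With no season at all, the two terms raised the V1-versus-V4 SE from 0.448 to 0.461, about 3%.

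**6. In terms of power.** At N = 80, f = 0.10 and 24 measures, unabsorbed season adding 10%, 20% or 30% to within-subject error variance lowers power from 0.84 to 0.79, 0.74 or 0.69. If the assumed f already includes seasonal noise in its SD, nothing is lost against the planned power.

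**The case against.** The strongest reply is that the conflict is read from silence. The article does not say that the ANOVA excludes covariates or that its time factor is study month. The Methods section says the analysis "will be guided by a pre-specified statistical analysis plan", which is not shown, and covariate lists and time coding usually belong there. This limits the point: the ANOVA names no calendar term, and a reader who infers that it is stated to have none goes beyond the text. It does not remove the point, because the article does commit to a model class, and that class in its standard form does not accommodate what the Study design section promises.

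Second, mixed models are already mentioned, and for monthly ACT explicitly. That stands, and ACT is outside the point. For the other outcomes, the general sentence leaves unclear which model is primary.

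Third, Table 1 plans 24 monthly values and participation is for two years; with 12 + 12 months season cancels. That holds for homes that achieve it, but the stated dates rule it out for late entrants. It is also true that recruitment dates are not V1 dates. If V1 were bunched, the time factor would absorb much or all of the season. The loss is therefore conditional on staggered starts.

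Two stronger readings are tempting. A reader might infer bias in active versus sham; randomised arms share the same seasonal mix, and none was found. Chance imbalance in start season is not a further cost either, since the standard error already reflects it. A reader might also apply the loss for a 5-month pre-period to every home: at amplitude 0.5 SD, with total SD 1 and within-home correlation 0.5, the variance ratio would be 1 + 0.068/0.142 = 1.48. The documents do not support a uniform short pre-period, and that figure is for monthly data, which among these outcomes fits only sensor IAQ.

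**Conclusion.** The point holds in a limited form. The seasonal covariates promised under Study design are not carried into the ANOVA named as primary for IAQ, mold, ACQ and spirometry, and that model is a poor vehicle for them. The trial's own dates make truncated pre-periods unavoidable for homes entering after about February 2026.

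The consequence is avoidable loss of precision, plus possible seasonal artefact in within-arm before-after statements. Under the assumptions shown, the standard error rises by about 5–8% (amplitude 0.5 SD) to 18–20% (1 SD) for monthly data, and by about 7–10% to 25–28% for V1 versus V4. The amplitude, the spread of starts and the distribution of pre-period lengths are all assumed. ACQ and spirometry, with four visits, were not computed separately. This is a cheap improvement, not a defect that invalidates the comparison.

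**What to change.** Reconcile the Study design section with the two statements on models in the analysis section by naming the primary model for each outcome. For IAQ, mold, ACQ and spirometry, replace the ANOVA with a mixed model:

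- random effects for home and, where several people share a home, for person;
- arm-by-period as the effect of interest;
- calendar time as a fixed effect, taken from the actual measurement date rather than the visit number: sine and cosine of the date, or calendar-month indicators where the data allow.

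State that the monthly ACT model carries the same term, and base before-after statements within an arm on the season-adjusted model.

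The cost is analysis wording and about two parameters in the sine/cosine form, using measurement dates. For outcomes with only 2 to 4 measurements this is a minor loss of degrees of freedom, about 3% on the V1-versus-V4 standard error if there is no season at all. Month indicators would cost more and suit only the monthly series. The article says data collection has not begun, so the change can still be prespecified.
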